## Abstract

**Background/Objectives**: The global spread of carbapenem-resistant *Pseudomonas aeruginosa* (CRPA) warrants collaborative action. Guidance should come from integrated One Health surveillance; however, a surveillance strategy is currently unavailable due to insufficient knowledge on the sources and transmission routes of CRPA. The aim of the SAMPAN study (“A Smart Surveillance Strategy for Carbapenem-resistant *Pseudomonas aeruginosa*”) is to develop a globally applicable surveillance strategy. **Methods**: First, an international cross-sectional study will be conducted to investigate CRPA in clinical and environmental settings in Rotterdam (The Netherlands), Rome (Italy), and Jakarta (Indonesia). Screening cultures and risk factor questionnaires will be taken from healthy individuals and patients upon hospital admission. Clinical CRPA isolates will also be included. Additionally, samples will be taken twice from wet hospital environments and monthly from the hospitals’ (drinking) water system, hospital and municipal wastewater treatment plants, and receiving rivers. Whole-genome sequencing will be performed to characterize CRPA isolates and determine the genetic relatedness among the isolates from different reservoirs. Findings from the cross-sectional study, combined with expert elicitation using a Delphi method, will serve as the input for the surveillance strategy. **Conclusions**: The SAMPAN study will provide a broader understanding of the sources and transmission routes of CRPA. Therewith, the development of a globally applicable smart surveillance strategy will be made possible, delivering information that is needed to guide actions against the spread of CRPA.

## 1. Introduction

Antimicrobial resistance (AMR) is an increasing global health challenge. In 2019, 1.27 million deaths worldwide were attributable to AMR, a number expected to increase to about 10 million annual deaths by 2050 [1,2]. One of the leading pathogens responsible for these deaths due to AMR is *Pseudomonas aeruginosa* [1]. Especially, infections with carbapenem-resistant *P. aeruginosa* (CRPA) are difficult to treat, cause a high disease burden, and are associated with an all-cause mortality rate of 30% and higher [1,3,4,5]. Consequently, the World Health Organization (WHO) has classified CRPA as a high-priority pathogen in their 2024 list, requiring urgent attention and action [3].

To design and focus such action, information from an integrated global surveillance strategy following a transdisciplinary One Health approach is needed, as antimicrobial-resistant bacteria do not only arise in and spread among humans. An example of such an integrated surveillance strategy that has proven to be useful is the WHO Tricycle protocol for extended-spectrum beta-lactamase (ESBL)-producing *Escherichia coli* [6,7,8]. However, it is likely that the sources and transmission routes are different for CRPA compared to ESBL-producing *E. coli*, which may require an emphasis on other key elements of such a surveillance strategy.

The human–water interface plays a fundamental role in the spread of CRPA, as these bacteria prefer moist environments. Inside of hospitals, transmission of CRPA from wet environmental niches, such as faucets, sinks, and showers, to hospitalized patients can occur and is estimated to account for over 85% of transmission events [9,10,11]. Patients colonized or infected with CRPA may, in turn, cause persistent environmental contamination in the hospital setting and/or transmission to other patients. Most of the reports on the environmental reservoirs and transmission pathways of CRPA inside of hospitals are derived from outbreak settings in high-income countries [9]. However, the role of environmental sources in the spread of CRPA in non-outbreak and low-resource settings is largely unknown.

Through human feces, CRPA may disseminate from the treated or untreated effluent of hospital or municipal wastewater treatment plants (hWWTPs/mWWTPs) into the aquatic environment outside of hospitals, including rivers, lakes, and coastal waters [12,13,14]. Also, the horizontal transfer of carbapenem resistance genes may further promote the development and spread of CRPA in sewage systems and receiving waters. Consequentially, the aquatic environment may function as a source of CRPA spread and poses a threat to public health, especially when sewage effluents are discharged in the environment untreated and humans depend on these receiving waters for drinking, washing, and sanitation [15]. Data on the carriage rates of *P. aeruginosa* in healthy individuals range from 1.5% to 15.8%, yet recent data on CRPA in healthy individuals and risk factors are lacking [16,17,18,19,20,21]. Also, to what extent contaminated (surface) waters contribute to the spread of CRPA in humans, and to what extent human and environmental isolates are genetically related and carry similar resistance genes and/or mobile genetic elements, is largely unknown. While various sources and transmission routes of CRPA, both inside and outside of hospitals, have been identified, the development of an integrated global surveillance strategy is hindered by multiple knowledge gaps (Figure 1).

In the SAMPAN study (“A Smart Surveillance Strategy for Carbapenem-resistant *Pseudomonas aeruginosa*”), we aim to develop a globally applicable smart surveillance strategy to guide actions against the spread of CRPA. Prior to formulating such a strategy, an international cross-sectional One Health study will be conducted to investigate the carriage rates, risk factors for carriage, and relevant sources and transmission routes of CRPA in different settings, with a particular emphasis on the human–water interface (Figure 2).

The specific aims of the international cross-sectional One Health study are as follows:Determine the carriage rates of CRPA and the risk factors for carriage in healthy individuals and patients at the moment of their admission to the hospital.Gain insight into the potentially relevant niches of CRPA in the moist environments of hospitals in different settings (non-outbreak, and high- and low-resource settings), as well as in (surface) water inside and outside of hospitals in three cities with different climates and water management systems.Unravel the genetic relatedness of CRPA in terms of clonality, resistance genes, and mobile genetic elements within the different reservoirs and climates in order to confirm possible transmission routes.

Subsequently, the findings of the international cross-sectional One Health study, together with expert opinion, will be used as the input in a Delphi method to develop the globally applicable smart surveillance strategy for CRPA.

## 2. Materials and Methods

### 2.1. Study Design and Setting

The initial phase of the SAMPAN study involves conducting a multicenter, cross-sectional One Health study. In this study, we will investigate the carriage rates, risk factors for carriage, and relevant sources and transmission routes of CRPA in humans and the environment. The study will take place in the following three countries: the Netherlands, Italy, and Indonesia. The selection of these countries is based on differences in climate, water management approaches, and the anticipated CRPA prevalence, thereby, providing the opportunity to study the sources and transmission routes of CRPA in various settings (Figure 3).

One hospital per country will be involved in this study (Table 1), including the Erasmus MC University Medical Center (Rotterdam, The Netherlands), Fondazione Policlinico Universitario Agostino Gemelli IRCCS (Rome, Italy), and [name] General Hospital (Jakarta, Indonesia). Samples will be collected from a variety of reservoirs in each city during a period of 12 months, including from healthy individuals, patients upon their admission to the hospital, clinical isolates, wet hospital environments, and water from each hospital’s (drinking) water supply system, hWWTP(s) and mWWTP, and the receiving river. The Medical Ethics Review Committee of each participating hospital gave written approval to conduct the study. This study was registered in ClinicalTrials.gov (registration number: NCT05282082).

### 2.2. Study Population and Recruitment Process

Firstly, we will enroll healthy individuals (i.e., not hospitalized) in each city over a period of one year. We aim to reach a total of 500 participants; however, formal sample size calculations cannot be performed due to the unknown CRPA prevalence in healthy individuals. To determine which healthy individuals to approach for study participation, certain “high-risk areas” were first mapped out for each city. A “high-risk area” is defined as an area that is expected to potentially have a high prevalence of CRPA which may affect humans because of being immediately downstream of the sewage systems of hWWTPs and/or mWWTPs. All of the healthy adult individuals living in these “high-risk areas” are eligible for inclusion in the study and can only participate once throughout the study period.

At first, individuals living closest to the river (<50 m) will be invited to participate either by a home visit from a member of the research team or by receiving a letter in the mailbox, followed by individuals living further away (<100 m). In case this method appears insufficient to recruit healthy individuals, the area will be expanded and different recruitment strategies will be explored, such as using social media, local newspapers, radio stations, and/or other live events to request healthy individuals to participate. Expanding the distance between residential addresses and the river may impact the results; however, whether there will be an effect, and what kind of effect, is currently unknown. We hypothesize that individuals residing nearest to the river may face a higher risk of becoming colonized by CRPA if the river is contaminated with CRPA and if these individuals (frequently) interact with the contaminated river.

Secondly, we aim to enroll 500 hospitalized patients in each city over a period of one year. Similarly, the lack of prevalence data among newly hospitalized patients prevents accurate sample size determination. Patients will be asked to participate within the first 48 h of their admission to the hospital. All of the patients from non-critical medical and surgical wards are eligible for inclusion if they are aged 18 years or older, if they have an expected length of stay of at least 24 h, if they can provide answers to a questionnaire verbally or in writing, and if they have a signed informed consent sheet. Patients will only be included once during the inclusion period. Patients that are unwilling to provide a rectal/perianal swab and patients with cystic fibrosis (CF) are excluded from study participation. The enrolment progress of healthy individuals and newly hospitalized patients will be monitored closely by the central study coordinators ([name] and [name]) in order to ensure the highest possible number of participants.

Clinical CRPA isolates from patients throughout the entire hospital, as identified through routine diagnostics, will also be collected. Only one CRPA isolate per patient will be included. If multiple CRPA isolates are available from the same patient, the first isolate will be included. If more than one isolate is available from that same date, the most resistant CRPA isolate (i.e., the highest MIC and/or resistance to a wider range of antibiotics) will be included. Clinical CRPA isolates from CF patients are not eligible for inclusion.

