#### 2.4.7. Statistical Analysis

Analyses will be performed using IBM SPSS Statistics (Version 28.0.1.0) and R software (Version 4.3.2), with MPN calculations performed by using the R package ‘MPN’. For descriptive purposes, continuous variables will be presented as means with standard deviations or medians with range, and categorical variables will be presented as absolute numbers with percentages. Risk factors and protective factors for CRPA carriage will be determined using (logistic) regression analysis on different patient characteristics. Factors will be included in the model based on expert opinion and as suggested by the univariate analysis. The number of variables which can be selected for the model depends on the number of CRPA cases found. Sex-based as well as seasonal analyses will be performed. Possible interactions will be explored by comparing models with and without interaction terms using the likelihood ratio test. Non-linear effects exploration will be performed if continuous variables are included. A two-sided *p*-value of <0.05 will be considered statistically significant.

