The multicenter design of the international cross-sectional One Health study with three sampling sites in different countries with anticipated differences in the prevalence rates of CRPA, and different climates and water situations, enables us to investigate the sources and transmission dynamics of CRPA in a variety of settings. The sources and transmission routes identified by this study will, therefore, also be relevant for many other countries around the world. Additionally, CRPA will be studied in clinical and environmental settings for the duration of one year, allowing us to examine the seasonality of CRPA carriage, the concentrations of CRPA in (waste)water, and CRPA transmission. Also, the extensive questionnaire used for healthy individuals, patients, and, when possible, for patients from whom clinical CRPA isolates are collected will identify potential risk factors for CRPA carriage. Furthermore, the in-depth genomic analyses using the latest technological advances will offer us the means to explore the molecular epidemiology of CRPA across the three cities, and will identify known and potentially also new genes encoding for carbapenem resistance. Finally, developing a surveillance strategy involves making trade-offs between comprehensiveness (i.e., including all relevant reservoirs, frequent sample collection, etc.) and efficiency in terms of time and cost. The findings of the international cross-sectional One Health study will provide indications as to which reservoirs are the most relevant for effective and efficient surveillance. Combined with expert opinion from across the globe, and building upon recommendations from the EPI-Net One Health consensus working group on multisectoral AMR surveillance reporting, as well as recommendations on developing One Health surveillance systems from the One Health High-Level Expert Panel, this will provide us the opportunity to formulate a surveillance strategy for CRPA that is both globally applicable and smart [38,39]. 

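### Inviting healthy residents outward from the river confounds river proximity with calendar time (and later with recruitment channel) where that order is followed, and no balancing over months is stated

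*Protocol article*

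**What the plan says.** Section 2.2 of the protocol article states that "we will enroll healthy individuals (i.e., not hospitalized) in each city over a period of one year", with a target of 500 and no formal calculation. Eligible adults live in mapped areas just downstream of wastewater discharge, and each may take part only once.

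The invitation order is explicit: "At first, individuals living closest to the river (<50 m) will be invited to participate", "followed by individuals living further away (<100 m"). If recruitment is insufficient, "the area will be expanded and different recruitment strategies will be explored", for example social media, newspapers, radio or live events. The section concedes that widening the distance may affect results, but does not mention calendar time.

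The same section gives a proximity hypothesis: "We hypothesize that individuals residing nearest to the river may face a higher risk of becoming colonized by CRPA", conditional on the river being contaminated and on contact with it. Section 2.4.7 adds: "Sex-based as well as seasonal analyses will be performed". The Discussion presents the one-year duration as "allowing us to examine the seasonality of CRPA carriage".

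Three further places bear on the point:
- **Section 2.3.1:** the distance computed for each healthy participant runs from the zip-code centroid to the municipal treatment plant and to the upstream and downstream river sampling points.
- **Table 2:** recruitment is by live events in Rome, home visits in Jakarta, and letters plus large-scale media requests in Rotterdam.
- **Sections 2.2 and 2.3.3:** 500 patients per city are enrolled over a year and water is sampled monthly. Neither is ordered by residents' distance from the river.

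**The concern.** If nearer residents are invited before farther ones, the near group is sampled on average earlier in the year. The conditional third step answers a shortfall, so it necessarily comes later, and it changes the recruitment channel as well as the distance. With one sample per person and one year of sampling, there is no within-person contrast and no second season to separate the two.

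A seasonal swing in carriage would then distort the comparison of near with far residents. If carriage is higher late in the year, farther residents look more at risk and a true river effect is masked. If it is higher early, the near-river hypothesis seems confirmed with no river effect present. In the same way, a true proximity effect would show as an apparent fall in carriage over the year among healthy residents.

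The model-building rule in Section 2.4.7 does not guard against this. Factors enter partly on the univariate analysis, where the distortion appears, and the number of variables is limited by the number of carriers.

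**Working it through.** The documents give no effect size, power or timing to reproduce. The check is how much spurious proximity effect the stated order can create under timings that the text allows.

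**From the article:** one-year enrolment, one participation each, order <50 m then <100 m then wider, target 500 (Section 2.2).

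**Assumed:** bands of equal size; no true distance effect; carriage differing between the two half-years, at 2% then 6%, or more mildly 1% then 2%. Carriage in healthy people is unknown, so these values are illustrative.

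**Formula.** If a share *s* of a band is sampled in the second half-year, its expected carriage is p = p1 + s(p2 − p1). The spurious odds ratio is the odds in the pooled farther bands divided by the odds in the nearest band. The variance inflation factor is 1/(1 − R²), with R² from regressing a nearest-band indicator on calendar quarter.

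| Timing of bands | s by band, near to far | OR at 2% v 6% | OR at 1% v 2% | Variance inflation |
|---|---|---|---|---|
| Two bands, strictly 6+6 months | 0; 1 | 3.13 | 2.02 | infinite |
| Three bands, strictly 4+4+4 months | 0; 0.5; 1 | 2.58 | 1.76 | 4.00 |
| Three bands, each open 8 months, starts 2 months apart | 0.25; 0.5; 0.75 | 1.52 | 1.30 | 1.30 |
| Three bands, starts 2 months apart, all left open | 0.5; 0.6; 0.75 | 1.18 | 1.12 | 1.10 |
| Three bands, starts 1 month apart, all left open | 0.5; 0.545; 0.6 | 1.08 | 1.05 | 1.02 |
| All bands invited every month | 0.5; 0.5; 0.5 | 1.00 | 1.00 | 1.00 |

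Worked examples at 2% v 6%:
- Strict 6+6: (0.06/0.94)/(0.02/0.98) = 3.13.
- Strict 4+4+4: the farther bands average (4% + 6%)/2 = 5%, so (0.05/0.95)/(0.02/0.98) = 2.58.
- One-month lag: the nearest band has 4%; the others have 4.18% and 4.40%, mean 4.29%. So (0.0429/0.9571)/(0.04/0.96) = 1.08.

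If the high-carriage half-year comes first, the direction reverses. For strict 6+6 the odds ratio becomes 0.32.

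**Can adjustment recover the effect?** In the strict 6+6 pattern, quarter determines band completely and the effects cannot be separated. In the strict 4+4+4 pattern, only the second quarter contains both nearest-band and farther residents, hence the fourfold inflation. With staggered bands left open, adjustment costs little variance. A smooth seasonal curve may return an estimate even without overlap, but that estimate then rests on the assumed shape of the curve.

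**Carriers available.** At an assumed carriage of 0.5% to 5%, 500 people yield 500 × 0.005 = 2.5 to 500 × 0.05 = 25 carriers. This takes the 500 as per city; if it covers all three cities, the count per city is lower.

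**The case against.** The strongest objection is that the timing is inferred. Section 2.2 gives an order but no dates or durations, and does not say that one band closes when the next opens. A reader might infer that neither the distance effect nor the seasonal effect can be estimated at all. The documents do not support that. It needs strictly consecutive bands with the change-over at a season boundary, and the second step could equally follow the first within weeks. This part stands and limits the point.

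Other objections stand in part:
- **City.** Table 2 lists only live events for Rome, and Rotterdam's media requests are not distance-ordered. The order is clearest for Jakarta home visits and Rotterdam letters.
- **Distance variable.** The computed distance is from zip-code centroid to sampling points, not to the river bank, so it maps only loosely onto the bands. This weakens the tie between the computed distance and calendar time. It also leaves the hypothesis about residents nearest the river without a matching recorded variable.
- **Reach.** Neither distance nor season is named in the specific aims, and the seasonal analyses are not confined to healthy residents. Patients and water give seasonal information that this order does not touch, but they do not estimate seasonality in healthy residents.
- **Few carriers.** With 250 per group and 2% v 1%, about 5 v 2.5 carriers are expected, and Fisher's exact test has power of about 7%. Sparse data may defeat either comparison whatever the order. That makes a confounded estimate no more interpretable.
- **Left to the analysis plan.** Covariate choice commonly is, and a joint model is possible under Section 2.4.7. Recruitment order, however, is fixed in this article, and no analysis can create overlap that was not sampled.

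**Conclusion.** The point holds in limited form. Among healthy residents, in cities where the outward order is followed, proximity to the river is confounded with calendar time, and also with recruitment channel once the area is expanded. Nothing stated keeps them apart.

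The size cannot be fixed from the documents. Under assumed carriage of 2% v 6% the spurious odds ratio runs from 1.08 (one-month lag, bands left open) to 3.13 (two strictly consecutive bands). At 1% v 2% the range is 1.05 to 2.02. The bias is negligible if the bands open close together and stay open, and becomes inseparable only under strict succession. If carriage does not vary by season, the order creates no spurious proximity effect. Conclusions about season in patients and water are unaffected.

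The change is worth making because it is cheap and can only be made while recruitment is under way.

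**What to change.** 1. **Invitation order (Section 2.2).** Each month, issue invitations in random order across both the <50 m and 50–100 m bands, instead of completing one before starting the next. If the area is later expanded, keep inviting from the nearer bands while eligible residents remain there. There is no need to hold back near-river residents in order to run expansion areas that may never be used.
2. **Data (Section 2.3.1).** Record each participant's bank-distance band, sampling date and recruitment channel. The zip-code-centroid distance does not capture the band.
3. **Analysis (Section 2.4.7).** Within each city, put band and a season term (one sine-cosine pair) in the same model and show the band-by-month table. Make no separate distance or seasonal claim for healthy residents where the two do not overlap. This also serves people already enrolled.

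**Cost.** The mailing or visit list changes and three items are recorded per person; the number of invitations stays the same. Near-river enrolment finishes later, and with few carriers the joint model will be imprecise.
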